#### **OBJECTIVES**

Implementing the proposed nutritional supplement in the routine care of GDH participants will:

1. test the feasibility, acceptance and compliance to the supplement and its safety
2. provide pilot data to test the superiority of the supplement versus an isocaloric placebo on measures of muscle mass, strength, physical performance, and mobility.

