**Intervention.** Participants will be screened and baseline measures will be performed within their first 3 visits to the GDH. Upon randomization, EXP group will ingest a supplement of flavored whey protein isolate with added pure leucine (3 g) twice daily, before breakfast and before bedtime. Doses are adjusted per body weight as follows: 20 g, 25 g or 30 g per category of <65 kg, 65-75 kg and >75 kg of body weight respectively (see Appendix Table 2 for nutritional details). Supplements will be offered during 8 weeks (average time of GDH program attendance) and for the following 8 weeks, at home or residence, for a total of 16 weeks. The CTR group will ingest an isocaloric placebo consisting of 30 g maltodextrin (a simple carbohydrate, providing 116 kcal), following the same schedule. Both products will be provided in pre-weighted doses in sterile containers; participants will be instructed to dilute and mix with 125 mL (1/2 cup) water to ingest. The fish oil + vitamin D supplement will be provided as a liquid oil (NutraSea Liquid® from Ascenta). Participants will receive a dosing cup, pre-marked to measure 7.5 mL, providing 1500 IU vitamin D3 + 1125 mg EPA + 750 mg DHA, to be ingested once daily. CTR participants will receive an isocaloric placebo oil (corn oil) to be ingested similarly. Oil supplements may be mixed with the protein or maltodextrin powders or ingested separately according to taste. Participants already taking vitamin D (at lower doses than indicated in exclusion criteria) or omega-3 FA supplements may take part in the study but will be asked to interrupt their supplements for the duration of the study. Compliance will be evaluated by twice-weekly monitoring during GDH visits and frequent phone calls during the

second half of study, by self-reporting in a logbook and return of all empty containers and extra oil; ingestion of 80% of provided doses will be required to remain in the study.

**Outcomes: all outcomes (except body composition) will be measured at baseline (prior to intervention), 8 weeks (last program visit) and 16 weeks (returning visit).**

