### ***Secondary outcome measures***

- ◆ Appendicular muscle mass index will be measured by dual energy X-ray absorptiometry (DXA) as the sum of arm and leg lean tissues (without bone mineral content) divided by height squared. This index defines sarcopenia. The test will be performed at the Montreal General Hospital or at the MUHC-McDonnell Centre for Innovative Medicine (Glen site).
- ◆ Voluntary physical activity measured by accelerometry. Participants will wear an ActiGraph® GT3X accelerometer (small belt-held device) during 4 days for each measurement. Instructions will be given on how and when to wear the device. The activity counts, energy expenditure, steps count, activity/sedentary bouts will be collected. An activity logbook will be completed during the same days.
- ◆ Food intake will be estimated from 3-day food diary. Instructions will be given on how to record food intake with portion size estimation with measuring cups and spoons, by a registered dietitian (PI or graduate student). Nutrient analysis will be performed using the Food Processor software (ESHA®).

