### **STATISTICAL ANALYSIS**

This is a pilot study designed to generate data on feasibility, acceptance and compliance to the supplement and study tests; it is not powered for identifying statistical differences in the main outcomes. The sample size required for the full study will be of approximately 160 participants (80 EXP, 80 CTR). This calculation is based on an expected difference of 1 second in reducing the chair-stand time between the 2 groups, acknowledging that the CTR will also gain from the rehab program, and from standard deviation from published studies. This sample size should be enough to detect differences in handgrip and leg strength and in appendicular muscle mass accretion. Pilot data will therefore be crucial to confirm these calculations. We aim to recruit 40 participants to provide confidence intervals to determine the final RCT sample size.

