### **ETHICAL CONSIDERATIONS**

All participants will provide written informed consent. Participants of both arms will benefit from a full nutritional counseling by the PI or the graduate student involved in this study, to optimize their nutritional intake in addition to the standard of care of the GDH program. Those randomized to the EXP group might further benefit from the supplement, in improving muscle mass strength and physical function, according to our hypothesis.

***Intervention products and doses:*** The whey protein isolate, leucine and maltodextrin (placebo) powders are commercially available for human use and safe to ingest at the proposed doses. All will be purchased from ProteinCo Canada, Cowansville, QC, which certifies a Pharmaceutical Grade Purity. These powders are fairly easy to dissolve in water with some mixing and have a sweet taste. The total amount of protein supplemented per day (36 g, 45 g or 54 g) will increase total daily protein intake to 1.2-1.5 g/kg/day, depending on current intake. This range is recommended by at least two international expert groups and recognized as safe for the older population. This dose is however not recommended for persons with severe kidney diseases; therefore, those having such diagnosis or an estimated glomerular filtration rate (eGFR) below 30 mL/min/SA will not be eligible to participate. The free leucine (3 g) added to the whey protein will total 6 g, twice per day = 12 g, which is below the tolerable upper intake level (UL) and safe limit in humans of >550 mg/kg/d, equivalent to 30-39 g/d depending on

weight. The leucine purity, of 99%, has been confirmed by LC-MS/MS and will be assessed for new lots purchased.

Vitamin D: the daily doses of  $\geq 1966.7$  IU (1966.7 IU, 1983.3 IU or 2100 IU depending on the body weight) of vitamin D3 is desirable to augment and reach serum 25(OH)D of  $\geq 80$  nmol/L, based on several studies mostly on osteoporosis and fractures; it is well below the tolerable upper intake level of 4000 IU/day (DRIs) for adults >70 years.

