## Appendix

**Table 1. Information on Dietary Supplements to be used**

| Supplement and ingredients                                                                                | Brand Name/Company                                             | Health Canada NPN | Daily Dose ingested                                                                                                   | UL                                    |
|-----------------------------------------------------------------------------------------------------------|----------------------------------------------------------------|-------------------|-----------------------------------------------------------------------------------------------------------------------|---------------------------------------|
| Experimental supplement                                                                     |                                                                |                   |                                                                                                                       |                                       |
| Whey protein isolate (vanilla flavored)

- Protein (27g/30g dose)
- Vitamin D3 (100 IU/30g dose) | New Zealand Whey Protein Isolate/ The Protein Company ATW Inc. | 80054732          | 2 x 20 g = 40 g
2 x 25 g = 50 g
2 x 30 g = 60 g

36 g
45 g
54 g

66.7 IU
83.3 IU
200 IU | N/A

4000 IU/d                  |
| Leucine                                                                                                   | ProteinCo Leucine Powder/ The Protein Company ATW Inc.         | 80062837          | 2 x 3 g = 6 g                                                                                                         | 550 mg/kg/d                           |
| Fish oil containing vitamin D (flavored) :
- EPA
- DHA
- Vitamin D3                              | NutraSea +D/ Ascenta                                           | 80050462          | 7.5 mL oil =

1125 mg
750 mg
1500 IU                                                                      | EPA + DHA :
5 g/d

4000 IU/d |

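### The powder placebo is one 116 kcal dose for everyone while the active powder is tiered by body weight, so it is not isocaloric below 65 kg

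*Protocol*

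**What the plan says.** Objective 2 of the Protocol (OBJECTIVES) is to "provide pilot data to test the superiority of the supplement versus an isocaloric placebo". The Intervention paragraph of METHODS then sets the two powders:

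- **Active:** "Doses are adjusted per body weight as follows: 20 g, 25 g or 30 g per category of <65 kg", with 25 g for 65–75 kg and 30 g above 75 kg. Each dose carries 3 g of added leucine whatever the weight and is taken twice daily.
- **Placebo:** "The CTR group will ingest an isocaloric placebo consisting of 30 g maltodextrin (a simple carbohydrate, providing 116 kcal", on the same schedule, with no weight tier.

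Appendix Table 1 shows the same asymmetry. It lists three daily amounts of whey (40, 50 and 60 g) and one daily amount of maltodextrin (60 g). It also gives the protein content of the whey: "Protein (27g/30g dose". ETHICAL CONSIDERATIONS agrees with that ratio: "The total amount of protein supplemented per day (36 g, 45 g or 54 g".

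The oil has its own control: "CTR participants will receive an isocaloric placebo oil (corn oil) to be ingested similarly". Active and placebo oil are both 7.5 mL daily, and that pairing is not in question.

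**The concern.** The active powder changes with body weight and the placebo powder does not, yet the Protocol calls the placebo isocaloric without qualification, both in the objective and in METHODS. A comparator with one fixed energy content cannot equal three doses with different energy contents.

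The purpose of an isocaloric control is to keep a difference in supplemental energy out of the comparison. If the match fails in one weight tier, the comparison there mixes the nutrients under test with a difference in energy, and a report that repeats the word would describe the comparator wrongly for those participants. The pilot is also meant to prepare a larger trial, which could inherit the mismatch.

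**Working it through.** **Inputs from the Protocol**

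- Whey per dose: 20, 25 or 30 g (METHODS, Intervention).
- Leucine per dose: 3 g in every tier (METHODS; Appendix Table 1).
- Protein content of whey: 27 g per 30 g, or 90% (Appendix Table 1).
- Placebo: 30 g maltodextrin, 116 kcal per dose (METHODS; 2 × 30 g daily in Appendix Table 1).

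**Assumptions**

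The text at hand gives no energy value for the active powder. METHODS refers to an Appendix Table 2 that is not in it, and no criticism is made of that. Protein and leucine are taken at 4 kcal/g. The 10% non-protein remainder is taken at 0 to 4 kcal/g, with 9 kcal/g (all fat) as an extreme bound.

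**The Protocol's own figure**

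116 / 30 = 3.87 kcal/g. At 4 kcal/g, 30 g would give 120 kcal, so 116 kcal is a plausible value for the placebo dose.

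**Energy of the active dose**

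Energy = 4 × (protein + 3) + r × remainder, with r = 0, 4 or 9.

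| Weight | Protein (g) | Remainder (g) | r = 0 | r = 4 | r = 9 |
|---|---|---|---|---|---|
| <65 kg | 18 | 2 | 84 | 92 | 102 |
| 65–75 kg | 22.5 | 2.5 | 102 | 112 | 124.5 |
| >75 kg | 27 | 3 | 120 | 132 | 147 |

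**Daily difference, control minus active, at full adherence**

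Difference = 2 × (116 − active energy), in kcal/day.

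| Weight | r = 0 | r = 4 | r = 9 |
|---|---|---|---|
| <65 kg | +64 | +48 | +28 |
| 65–75 kg | +28 | +8 | −17 |
| >75 kg | −8 | −32 | −62 |

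Below 65 kg the active dose therefore has less energy than the placebo by 32/116 = 28%, 24/116 = 21% or 14/116 = 12%.

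**Check that does not depend on leucine**

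The heaviest tier receives 10 g more whey than the lightest: 9 g protein and 1 g remainder. That is 9 × 4 + 1 × (0 to 4) = 36–40 kcal per dose, or 72–80 kcal/day. Leucine is the same in every tier and cancels, so no energy value for it lets one placebo match all three.

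**How far the assumptions would have to move**

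For the lightest tier's 23 g (20 g whey plus 3 g leucine) to reach 116 kcal, the mixture would need 116 / 23 = 5.04 kcal/g. With protein at 4 kcal/g, leucine alone would have to supply (116 − 72 − 8) / 3 = 12 kcal/g with the remainder at 4 kcal/g, or (116 − 72 − 18) / 3 = 8.7 kcal/g with the remainder all fat.

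**The case against.** The strongest reply accepts the asymmetry and disputes its size and weight.

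- **The gap is assumed, not read.** Appendix Table 2 may list the energy of each active dose. That could change the size of the gap but could not make one placebo equal three doses.
- **Leucine's energy value is itself uncertain.** At an illustrative 6 kcal/g, the active dose below 65 kg becomes 90–98 kcal and the gap +36 to +52 kcal/day, or +16 with an all-fat remainder. This stands: 21–28% is conditional on 4 kcal/g. The sign does not change.
- **The objective covers the whole supplement, oil included.** Assuming about 62 kcal/day of matched oil, the lightest tier compares 230–246 with 294 kcal/day, which is 16–22% less. That is a fair alternative denominator; the absolute gap is unchanged.
- **Little hangs on it.** Of the study, the Protocol says "it is not powered for identifying statistical differences in the main outcomes", and the target is 40 participants. The feasibility outcomes do not turn on some 50 kcal/day, and the Protocol records diet: "Food intake will be estimated from 3-day food diary". This also stands, and it is why the point is minor.
- **Gram figures for new fills are no firmer than the assumptions.** Correct: with an all-fat remainder, fills of 23, 28 and 33 g leave −26, −32 and −39 kcal/day, and the middle tier would be worse than now (−17). With leucine at 6 and the remainder at 4 kcal/g they leave about −18, −19 and −21. The labelled energy should govern.

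The word could be read as an approximate or average match. The Protocol does not say so, and it gives no distribution of participants across tiers to support an average.

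**Conclusion.** The point holds and is minor. A fixed 116 kcal placebo is set against three active doses about 36–40 kcal apart, so the unqualified claim of equal energy cannot be true in every tier. It fails most clearly below 65 kg, where control participants receive about 48–64 kcal/day more than active participants; with an all-fat remainder the figure is 28. The middle and upper tiers are roughly matched.

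Confidence is high for the direction below 65 kg. The size depends on the assumed energy factors and on full adherence. No trial-wide figure is offered, because the share of participants in each tier is not given. Any effect on muscle or performance outcomes is probably small and has not been quantified. No unblinding is claimed.

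**What to change.** **Preferred.** Fill the maltodextrin in the same three weight tiers, matched to the labelled energy of the active powder including leucine. At 3.87 kcal/g, the assumptions with the remainder at 0–4 kcal/g give about 22–24 g (<65 kg), 26–29 g (65–75 kg) and 31–34 g (>75 kg). Fills of 23, 28 and 33 g would serve, and they also equal the active powder mass in each tier (20 + 3, 25 + 3, 30 + 3). They supply 88.9, 108.3 and 127.6 kcal, leaving control minus active at −6 to +10, −7 to +13 and −9 to +15 kcal/day. These weights are illustrative until checked against the label.

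**Alternative.** Keep the single 30 g dose, drop the word isocaloric for the powder placebo in OBJECTIVES and METHODS, leave the corn-oil wording as it is, and report the energy difference by weight tier.

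**Cost.** Three fills of the same powder in containers that are already pre-weighed, plus a short amendment. No new visits or participants. The alternative costs only the amendment and a line in the report.

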## BACKGROUND

Malnutrition is highly prevalent in the elderly population, ranging from 5-10% in community-dwelling individuals to more than 50% in hospitalized patients and those in rehabilitation and long-term care. Our prior study (funded by the Helen McCall Hutchison Foundation) of frail elderly patients enrolled in the MUHC-Geriatric Day Hospital (GDH) rehabilitation program revealed that 6% of new attendees were frankly malnourished, an additional 13% were moderately malnourished and overall, 53% were at risk of malnutrition. Malnutrition was associated with lesser muscle and fat mass, and handgrip strength, a measure of muscle strength. Scores of malnutrition (from the Mini-Nutritional Assessment, MNA) correlated with gait speed, a strong indicator of physical performance, mobility and even morbidity. These findings justify testing a nutritional intervention aiming at improving nutritional status and physical performance of the GDH participants.

The comprehensive GDH program includes individualized physiotherapy, occupational health, nursing and medical care for rehabilitation of patients with loss of autonomy after hospitalization, falls, or rapid decline in their ability to perform activities of daily living. Unfortunately, no dietetic counseling is offered as part of the program. Therefore, for an eventual implementation of the program, our proposed intervention has to be pragmatic, feasible and targeted towards the main nutrients known to affect physical functioning, namely protein and vitamin D and possibly omega-3 fatty acids.

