*Dietary Protein Recommendations and Supplements.* The official Recommended Daily Allowance (RDA) of protein for the elderly is currently actively debated and the suggestion to revise it upward is endorsed by many experts. All acknowledge that the RDA should not merely cover the minimal protein needs to avoid deficiency but rather, the amount to minimize lean tissue loss, sustain optimal health and maintain an active living. In the Health, Aging and Body Composition study including 2066 men and women of 70-79 years, the loss of total lean and appendicular muscle mass was less in the highest quintile of energy-adjusted protein intake of 1.2 g/kg/d than in the lowest quintile of 0.8 g/kg/d. Likewise, analysis of a subset of the Women's Health Initiative study (n=24,417 women, 65-79 years) determined a 32% lower risk of developing frailty over 3 years associated with a 20% increase in calibrated protein intake (as % of energy). From these and other studies, a protein intake of at least 1.2 g/kg/day should be advised.

The positive impact of protein supplementation on increasing gains in muscle mass and strength during prolonged resistance-type exercise is well demonstrated in young and older adults. However, the role of protein supplement alone, in persons who cannot or do not want to engage in such exercise is more mitigated and may largely depend on protein quality, dose and the timing of ingestion. Dietary protein contain non-essential and essential amino acids (AA), the latter recognized to be responsible for stimulating muscle protein synthesis and the post-prandial anabolic response. Leucine is the most potent amino acid capable of stimulating protein synthesis through signaling to the intracellular nutrient-sensing mTORC1 resulting in increased mRNA translation and protein elongation. We and others have proposed that a significant increase of circulating leucine is necessary to illicit anabolic effects in

muscle, the so-called anabolic threshold, which is elevated in older and particularly frail persons due to associated conditions such as inactivity, insulin resistance and inflammation.

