## METHODS

**Participants.** All newly admitted patients, men and women, referred to the GDH program (of the MGH) who meet eligibility criteria will be invited to participate. Participants must be able to understand study requirements (Mini Mental State Exam, MMSE >22/30) and to read and speak English or French. Participants with the following criteria: BMI >35 kg/m^2, presence of kidney (GFR <30 mL/min/SA), liver or heart failure, stroke in the last 6 months (unless totally recovered), Parkinson's disease, severe neurologic conditions, active malignancies, acute inflammation (CRP >10 mg/L), known diagnosis of hyperparathyroidism, recent acute weight loss (>10% in 3 months, unless stabilized), allergy to milk and/or fish, long-term use of corticosteroids or anti-neoplastic medication, will be excluded from the study. All subjects taking vitamin D supplements  $\geq$  800 IU/d will be asked to reduce their dose to 400 IU/d. If vitamin D supplements were prescribed, the subjects' physician will be informed to change the current prescription to 400 IU/d for the study duration. As for subjects taking any type of omega-3 supplements, they will be asked to cease it for the study duration. All eligible subjects will be approached by the study coordinator and will be provided with an information brochure. Subjects interested in participating will be invited to review study procedures and sign the consent form.

**Study design.** This is a randomized, placebo-controlled, double-blinded pilot trial of two parallel arms. Participants will be randomly assigned to one of two groups: experimental (EXP) or control (CTR). Randomization will be achieved by computer-generated permuted block of 4 with stratification according to sex. Research staff and participants will be blinded to group allocations.

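### Eligibility has no glycaemic limit, so a patient with poorly controlled diabetes can be randomised to 60 g/day of maltodextrin placebo for 16 weeks

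*Protocol*

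**What the plan says.** **Placebo.** Under METHODS, Intervention, controls receive an "isocaloric placebo consisting of 30 g maltodextrin (a simple carbohydrate, providing 116 kcal), following the same schedule". The schedule is two intakes a day, and Appendix Table 1 confirms the 60 g daily total. Dosing runs through the 8-week programme and then "for the following 8 weeks, at home or residence, for a total of 16 weeks".

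**Eligibility.** METHODS, Participants lists the exclusions. Two carry numeric blood limits: "presence of kidney (GFR <30 mL/min/SA), liver or heart failure" and "acute inflammation (CRP >10 mg/L". The list ends with "allergy to milk and/or fish, long-term use of corticosteroids or anti-neoplastic medication, will be excluded from the study". Diabetes, glucose, A1C and glucose-lowering drugs do not appear.

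**Safety text.** ETHICAL CONSIDERATIONS, Intervention products and doses, describes the whey, leucine and maltodextrin powders as safe at the doses chosen. The same paragraph warns against the protein dose in severe kidney disease and turns that warning into an eGFR exclusion. It names no group for which maltodextrin needs care. The side effects and risks described after it are fishy aftertaste, burping and gastrointestinal changes.

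**Population.** BACKGROUND refers to "frail elderly patients enrolled in the MUHC-Geriatric Day Hospital (GDH) rehabilitation program" and says that the anabolic threshold is "elevated in older and particularly frail persons due to associated conditions such as inactivity, insulin resistance and inflammation".

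**Blood tests and care.** METHODS, Other measures and questionnaires, lists A1C, glucose and insulin, and notes that the panel is largely routine at the GDH. No limit or action is attached to these results. The GDH programme supplies "individualized physiotherapy, occupational health, nursing and medical care".

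**The concern.** The protocol asks of the protein dose whether any group should not take it, and writes the answer into eligibility. It does not ask the same of the carbohydrate given to the other arm. Someone with poorly controlled diabetes who meets the remaining criteria is eligible and has a one-in-two chance of the maltodextrin arm.

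Patient safety is at stake, and safety is part of the first objective. The exposure comes from a placebo powder from which the participant is expected to gain nothing, and half of it falls after programme visits have ended. The protocol itself names insulin resistance among the conditions that accompany frailty, so the question could have been foreseen from its own text.

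**Working it through.** **1. The plan's own dose.** Inputs: 30 g and 116 kcal per intake, twice a day (METHODS, Intervention).
- Powder: 2 × 30 g = 60 g/day, which reproduces Appendix Table 1.
- Energy: 2 × 116 = 232 kcal/day.

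**2. Carbohydrate content.** The text shown gives none for the placebo, so 4 kcal/g is assumed.
- Per dose: 116 / 4 = 29 g.
- Per day: 2 × 29 = 58 g. The powder weight sets the ceiling at 60 g/day, so the range is narrow.
- A participant who just meets the 80% ingestion rule still averages 0.8 × 60 = 48 g/day of powder.

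**3. Share at home.** 8 of 16 weeks = 50%.

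**4. Does any stated rule keep the patient out or lead to action?**

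| Place in the protocol | What it provides | Glycaemic rule? |
|---|---|---|
| Participants | Exclusions, with numeric limits for GFR and CRP | None |
| Intervention | Twice-weekly monitoring, then phone calls, described as compliance checks | None |
| Outcomes schedule and Other measures | A1C, glucose and insulin among the bloods | Measured; no limit, no action |
| Intervention products and doses | Powders safe at the chosen doses; kidney caveat for protein | No caveat for maltodextrin |
| Potential risks | Gastrointestinal effects; adverse events recorded; a study physician mentioned | Hyperglycaemia not named |

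No row excludes the patient, and no row says what happens if the result is high.

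**5. Would an exclusion be workable?** Screening and baseline measures come before randomisation, and the GFR and CRP limits already require blood results by then. A glycaemic limit can be applied at the same point.

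**6. Stopping for safety under the present rule.** Participants must take 80% of doses to stay in the study. Someone with perfect adherence who stops at week 8 has taken 8/16 = 50% of the full course, below 80%. Read over the whole course, the rule removes that person from follow-up.

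**The case against.** The case on the other side is substantial.

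- **No internal contradiction.** Diabetes is never mentioned. Insulin resistance is cited to explain the response to leucine, not tolerance of carbohydrate. That this load would worsen poorly controlled diabetes is a clinical judgement, and the documents give no effect on glucose or A1C. This stands and limits the weight of the point. It does not remove the gap, because the protocol treated the protein dose with exactly this kind of judgement.
- **The safety statement is qualified.** A reader might infer that maltodextrin is declared safe without any qualification. The text does not support that: the statement is tied to the proposed doses. What is missing is a caveat about population.
- **Glycaemia is not ignored.** A reader might also infer that nothing is measured after baseline. The outcome schedule covers baseline, 8 and 16 weeks with body composition as its only exception, and most naturally includes the bloods. The panel is largely routine at the GDH, although the text does not say whether A1C is. Patients receive medical and nursing care, and both arms receive nutritional counselling from dietitians. These safeguards reduce the risk, but none is tied to a limit or a decision.
- **The size of the risk is unknown.** The prevalence of diabetes among GDH patients is not given, so no count of affected participants can be supported. Multiplying the daily dose into a 16-week total would not measure risk either.

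**Conclusion.** The point holds as a gap in eligibility and safety wording. As written, the protocol permits a patient with poorly controlled diabetes to be randomised to 60 g/day of maltodextrin, about 58 g/day of carbohydrate, for 16 weeks, half of it at home. No stated result would prevent this or prompt a review.

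The conclusion rests on the absence of a glycaemic criterion from the exclusion list, on the assumed 4 kcal/g, and on the clinical judgement that such a load is undesirable in poorly controlled diabetes. It does not show that any participant would be harmed, or how many would be exposed. It concerns the protocol text only; the consent pages are not shown and may say more. Eligibility limits belong in a protocol, so the absence of an analysis plan does not excuse the gap.

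The change should be made because it is cheap and protects patients. Confidence is medium, since the existing clinical oversight may catch many such cases in practice.

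**What to change.** 1. **Participants:** exclude poorly controlled diabetes by a numeric A1C or fasting glucose limit. The study physician sets the limit before enrolment, and it is applied to the baseline bloods before randomisation, alongside GFR and CRP. This is the main protection, and the only one of the three that covers the first 8 weeks.
2. **Intervention and Other measures:** confirm that the 8-week bloods include A1C and glucose. Have the study physician review them before the home phase for participants with diabetes in either arm, which needs no unblinding. Exempt anyone who stops the powder on safety grounds from the 80% ingestion rule, so that they stay in follow-up. Without that exemption, the stopping provision would conflict with the rule.
3. **Ethical considerations:** add a diabetes caveat to the maltodextrin statement and list hyperglycaemia as a potential risk.

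**Cost.** Amendment wording, using tests and a physician already in the protocol. If the 8-week bloods were not meant to include A1C and glucose, one added test at an existing visit for participants with diabetes. Some otherwise eligible patients will be excluded. The number is probably small but cannot be computed from the documents, and the pilot population becomes slightly narrower.
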